## Abstract

**Background:**

Regular participation in physical activities is important for all children to stay fit and healthy. Children with cerebral palsy have reduced levels of physical activity, compared to typically developing children. The aim of the LEARN 2 MOVE 7-12 study is to improve physical activity by means of a physical activity stimulation program, consisting of a lifestyle intervention and a fitness training program.

**Methods/Design:**

This study will be a 6-month single-blinded randomized controlled trial with a 6-month follow up. Fifty children with spastic cerebral palsy, aged 7 to 12 years, with Gross Motor Function Classification System levels I-III, will be recruited in pediatric physiotherapy practices and special schools for children with disabilities. The children will be randomly assigned to either the intervention group or control group. The children in the control group will continue with their regular pediatric physiotherapy, and the children in the intervention group will participate in a 6-month physical activity stimulation program. The physical activity stimulation program consists of a 6-month lifestyle intervention, in combination with a 4-month fitness training program. The lifestyle intervention includes counseling the child and the parents to adopt an active lifestyle through Motivational Interviewing, and home-based physiotherapy to practise mobility-related activities in the daily situation. Data will be collected just before the start of the intervention (T0), after the 4-month fitness training program (T4), after the 6-month lifestyle intervention (T6), and after six months of follow-up (T12). Primary outcomes are physical activity, measured with the StepWatch Activity Monitor and with self-reports. Secondary outcomes are fitness, capacity of mobility, social participation and health-related quality of life. A random coefficient analysis will be performed to determine differences in treatment effect between the control group and the intervention group, with primary outcomes and secondary outcomes as the dependent variables.

**Discussion:**

This is the first study that investigates the effect of a combined lifestyle intervention and fitness training on physical activity. Temporary effects of the fitness training are expected to be maintained by changes to an active lifestyle in daily life and in the home situation.

**Trial registration:**

This study is registered in the Dutch Trial Register as NTR2099.

## Background

Regular participation in physical activities is important for all children to stay fit and healthy. This is especially important for children with disabilities, who are often restricted in their activity options due to mobility problems. Cerebral palsy (CP) is the most common cause of physical disability in pediatric rehabilitation medicine and describes a group of disorders of the development of movement and posture, causing activity limitation, that are attributed to non-progressive disturbances that occurred in the developing fetal or infant brain[1]. Despite the non-progressive character of CP some children deteriorate in mobility related activities during childhood[2]. Current insights suggest that interventions for school-age children with CP should focus more on promoting an active lifestyle and increasing physical fitness[3]. This is the starting point of the LEARN 2 MOVE 7-12 study, that will evaluate a physical activity stimulation program in children with spastic CP aged 7 to 12 years. The LEARN 2 MOVE 7-12 study is part of the Dutch national LEARN 2 MOVE research program[4-6].

Children with CP have reduced levels of physical activity[7] and fitness[8-10] compared to typically developing children. A decrease in the level of fitness may reduce physical activity in a child with CP, and vice versa, which may result in a downward spiral of loss of muscle strength, reduced fitness and mobility, and in the long term, secondary complications due to inactivity, such as fatigue, pain, overweight, and osteoporosis[11]. This downward spiral should be broken in order to maintain current and future physical activity. This is especially important for young children, since achieving an active lifestyle between 9 and 18 years of age improves their prospects for an active lifestyle during adulthood[12].

Recent studies have shown that fitness training can improve physical fitness in children with CP[13,14]. In the only study[15] in which the effect of fitness training on both fitness and physical activity was investigated, no effect was found on physical activity[15], despite increases in fitness. The lack of a lifestyle intervention might explain this lack of effect, because positive effects on physical activity have been reported in children with no disabilities who participated in physical activity interventions[16], as well as in adults with disabilities who received counseling to adopt an active lifestyle[17].

It has been reported that, in children with CP and in typically developing children, motivation[18] and parental support[18,19], as well as self-efficacy and parental physical activity[19] influence a more active lifestyle. It is therefore important that parents are also involved in the intervention. Moreover, restricted mobility has been shown to be an important factor that limits physical activity in children with CP[7]. It is expected that practising mobility-related activities in the daily environment will result in an increase in the capacity of mobility and, in turn, provide more physical activity options. Recent published work indicating the lack of transferral from the therapy setting to the home and daily life situation[20] emphasizes this need for home-based programs.

There seems to be a lack of knowledge concerning physical activity interventions that focus on all these aspects of lifestyle, fitness and mobility in children with CP. To our knowledge, the effects of such a combined intervention have not yet been studied in children with CP. Thereby, the effects of interventions have been mostly evaluated in standardized laboratory settings, instead of in daily life situations[21].

The main aim of the LEARN 2 MOVE 7-12 study is to improve physical activity in children with CP by means of a physical activity stimulation program, consisting of a lifestyle intervention and a fitness training program. A secondary aim is to investigate the effects of this physical activity stimulation program on fitness, capacity of mobility, social participation and health-related quality of life.

## Methods/Design

### Participants and recruitment

A total of 50 children, aged 7 to 12 years, with spastic CP and Gross Motor Function Classification Scale (GMFCS) level I-III, will be included in the study. Children are included if they fulfill at least one of the following three criteria: 1) they are less active than the international physical activity norm (moderately active for one or more hours per day), 2) they do not regularly participate in sports (less than three sessions per week for 20 minutes or more), 3) they have experienced problem(s) related to daily life mobility or sports. At least one of the parents must have adequate command of the Dutch language. Children are excluded if they have instable seizures, contra-indications for physical training (such as cardiac arythmia, mitochondrial defects, or hip dysplasia), behavioral problems interfering with participation in a group, or a predominant dyskinetic or atactic movement disorder. Children who have had surgery in the past six months, and botuline toxine treatment or serial casting in the past three months (or planned to take place during the intervention period) are also excluded. On enrollment, eligibility criteria will be checked by the research co-ordinater in a telephone interview.

Pediatric physiotherapy practices, special schools for children with disabilities, and services for ambulant care will be informed about the study and the inclusion criteria. If they agree to participate, they will send information about the study to potential participants and parents. Additionally, pediatric physiatrists and the Dutch Association of Physically Disabled Persons and their Parents (BOSK) will inform families about the study by means of a brochure. All participating parents (and children who are 12 years of age and over) must sign and return the informed consent form indicating voluntary participation in the study.

### Design

This study will be a 6-month single-blinded randomized controlled trial (RCT) with a 6-month follow up, that will be performed in special schools for children with disabilities and pediatric physiotherapy practices in the Netherlands, between September 2009 and February 2012. Within each school or practice, participants will be randomly assigned to either the intervention group or the control group. A blinded independent researcher will provide the allocation sequence in sealed envelopes. For schools and practices with five or more participants, children will be stratified for GMFCS level (I *vs*. II/III) before randomization. Group allocation will only be revealed to the parents after the baseline measurements. The assessors are blinded for group allocation during the entire study period. The children and parents will be instructed not to tell the assessors which group they are assigned to. The study protocol has been approved by the Medical Ethics Committee of the VU University Medical Center in Amsterdam.

### Procedure

Children in the control group will continue with their regular pediatric physiotherapy. Since the content and frequency of the regular pediatric physiotherapy may differ among children, the physiotherapists will keep diaries about the treatment goals, and the intensity and frequency of physiotherapy sessions. Additionally, the content of the regular pediatric physiotherapy will be objectively determined by means of video-taping at least one physiotherapy session of each child. The children in the intervention group will participate in a 6-month physical activity stimulation program, instead of their regular pediatric physiotherapy. This program consists of: 1) a lifestyle intervention, combined with, 2) a fitness training program (see Figure 1).

**Figure 1 F1:**
[figure not shown]
**Design of the LEARN 2 MOVE 7-12 study (intervention and measurements)**.

The data will be collected during a period of one year: just before start of the intervention (T0), after the 4-month fitness training program (T4; limited measures), after the 6-month lifestyle intervention (T6), and after six months of follow-up (T12). The primary outcomes are physical activity, measured with the StepWatch activity monitor, and self-reported physical activity. Secondary outcomes are fitness, capacity of mobility, social participation and health-related quality of life.

To describe the study population the disease and environmental characteristics of the child will be measured. Disease characteristics are determined according to the GMFCS level, the Functional Mobility Scale (FMS)[22], the Manual Ability Classification System [MACS])[23], unilateral or bilateral involvement, and selective motor control of the lower extremities[24]. Environmental characteristics include type of school, living environment (rural or urban), family structure, socio-economic status, parental stress and support[25,26], and parental physical activity.

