### Outcome measures

The primary outcome of this study is physical activity. Physical activity will be measured objectively with the StepWatch™Activity Monitor 3.0 (StepWatch) (Cyma Corporation Seattle WA, USA) as well as subjectively with self-reports: the Activity Questionnaire for Adults and Adolescents (AQuAA), and the Children's Assessment of Participation and Enjoyment (CAPE).

*The StepWatch *is an ankle-worn bi-axial accelerometer (frontal-sagittal plane) that registers the number of steps per minute. The StepWatch can accurately record steps for different gait styles, because the sensitivity settings are calibrated for each child individually. Before each registration period, the sensitivity settings will be calibrated by comparing manual counts of a 50-step walk with StepWatch recordings. The settings will be adjusted until an agreement of > 95% is reached between manual counting and the StepWatch registration. Children will wear the StepWatch for seven consecutive days during all waking hours, except when swimming and bathing. During the registration period, the parents will fill in a weekly diary to register the child's daily activities and the weather conditions. The StepWatch is valid for children with CP, and able to discriminate between activity levels of children with different GMFCS levels[7].

*The AQuAA *is a reliable questionnaire to assess physical activity as well as sedentary behavior[35] in adolescents and adults. It is derived from the valid and reliable Dutch Short Questionnaire to Assess Health-Enhancing Physical Activity[36], but questions about sedentary behaviours were added and the recall period was specified as "the past seven days"[35]. The parents will have to rate how many days, and how much time per day the child spent on transportation to and from school, activities at school and at home, as well as leisure time activities and sports in the past seven days. The parents will also have to indicate how strenuous (light/moderate/vigorous) these activities were. For the purpose of the present study the examples of activities will be adapted, so that they are relevant for school-aged children.

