*The CAPE *is a 55-item questionnaire that will be used to assess the frequency of participation in activities outside school hours[37]. The parents will be interviewed to rate the child's frequency of participation in the past four months in five types of activities (recreational, active physical, social, skill-based, and self-improvement activities). The frequency, scored on a 7-point scale, provides: a) the overall participation scores, b) the domain scores for formal and informal activities, and c) the scores for participation in each type of activity. The Dutch version of the CAPE is a valid and reliable questionnaire with which to assess the participation of children with disabilities aged 6-21 years[38].

Secondary outcomes are fitness, capacity of mobility, social participation, and health-related quality of life. Fitness is defined in this study as isometric muscle strength, aerobic capacity, anaerobic capacity, and anthropometry. Capacity of mobility is defined as gross motor functioning, functional muscle strength, and walking capacity. Health-related quality of life is as CP-related quality of life, self-reported fatigue, self-perception, and attitude towards physical activity.

*Isometric muscle strength *of the knee extensors and hip abductors will be assessed with a hand-held dynamometer (HHD)[39] (MicroFet, Biometrics, Almere) using the "make-method". The assessor stabilizes the dynamometer at the limb while the child pushes as hard as possible against the dynamometer for three seconds. Peak strength (N) is then read from the dynamometer, and the distance from the knee and hip joint to the dynamometer is measured to determine the lever arm. Moment is then calculated from peak strength and lever arm (Nm). After one practise trial, the children will perform three test trials. The means of the peak moment (Nm) over three trials will be used for the analysis. The testing positions and stabilization have been described in detail elsewhere[32].

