### Statistical analysis

A sample-size calculation revealed that at least 22 children in each group are required to detect a difference in improvement of 1,000 steps per day between the intervention and the control group on the primary outcome. The power was 0.8, and the alpha was set at 0.05. This increase in steps per day seems to be clinically relevant, since improved health outcomes have been reported in adults after an increase of 1,000 in the amount of steps per day[54]. Taking into account drop-outs, 25 children will be included in each group.

Student *t*-tests will be performed to evaluate group differences at baseline, and a random coefficient analysis[55] will be performed to determine differences in change over time (treatment effect) between the control group and the intervention group. This method takes the dependency of children within physiotherapy practices and schools into account. An intention-to-treat analysis will be performed. The primary outcome (physical activity) and secondary outcomes (fitness, capacity of mobility, social participation, and health-related quality of life) will be the dependent variables in the analysis, with group allocation (control group or intervention group) and measurement occasion (time) as independent variables. The intervention effect will be evaluated by the group * time interaction. The alpha is set at 0.05. The influence of age, gender, and disease and environmental characteristics on the treatment effect will be investigated, and, if necessary, included as covariates in the analysis. The data will be analyzed with the Statistical Package for the Social Science, version 15.0 (SPSS Inc, Chicago, Illinois, USA).

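### Three instruments share primary status with no order or success rule, but only StepWatch steps per day is powered and one unadjusted alpha of 0.05 is stated

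*Protocol article*

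**What the plan says.** The protocol article describes the primary outcome in three ways.

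- **Procedure** (and, in similar words, the Abstract) uses the plural: "The primary outcomes are physical activity, measured with the StepWatch activity monitor, and self-reported physical activity".
- **Outcome measures** uses the singular, "The primary outcome of this study is physical activity", and then says it is measured objectively with the StepWatch "as well as subjectively with self-reports: the Activity Questionnaire for Adults and Adolescents (AQuAA), and the Children's Assessment of Participation and Enjoyment (CAPE"). That makes three instruments. From the CAPE frequency ratings come "a) the overall participation scores, b) the domain scores for formal and informal activities, and c) the scores for participation" by activity type, and five types are listed. No score is named as the one that counts.
- **Statistical analysis** uses the singular again and ties it to the step count. It asks for 22 or more per group so as to "detect a difference in improvement of 1,000 steps per day between the intervention and the control group on the primary outcome". Power is 0.8 and alpha 0.05.

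The same section makes primary and secondary outcomes the dependent variables of one type of model, evaluates the effect by the interaction of group and time, and gives a single alpha of 0.05. It states no testing order, division of alpha or rule for success.

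Two other statements bear on the point. Under Design, parents learn the allocation after the baseline measurements and only the assessors stay blinded. Under Outcome measures, parents complete the AQuAA and are interviewed for the CAPE.

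**The concern.** The term primary outcome covers one, two or three things depending on the section. The stated alpha and power describe a trial with one primary variable, whereas the stated outcomes describe a trial with three. A reader of the results cannot tell from this article whether a positive AQuAA beside a null StepWatch would be a positive trial, a negative trial or a mixed one.

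The choice of lead measure matters more than usual here. StepWatch is recorded by a device. The AQuAA and CAPE are reports by parents who know the group and, in the intervention arm, have been counselled towards a more active lifestyle for their child. Blinding the assessor does not protect those answers. The two instruments without a power calculation are therefore also the two most open to reporting bias, and an unordered primary set lets either of them carry the conclusion.

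**Working it through.** **1. The plan's own figure.** Inputs from Statistical analysis: difference in improvement 1,000 steps per day, power 0.8, alpha 0.05, 22 per group. The SD and the sidedness are not given, so 22 cannot be verified independently; it can only be solved backwards. Assuming a two-sided test and the normal approximation:

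n per group = 2 × (1.96 + 0.842)² × SD² / 1000²

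This rounds up to 22 for an SD of change of 1,157 to 1,183 steps per day. At SD = 1,183: 2 × 7.85 × 1.3995 = 21.97, so 22. With the t distribution the range is 1,129 to 1,156. The calculation is thus consistent with a single two-sided test of steps per day at the full 0.05. No other instrument enters it.

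**2. False-positive rate if any one positive instrument counts.** This success rule is an assumption. With one test per instrument, each at 0.05, and no true effect:

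- Independent tests: 1 − 0.95³ = 1 − 0.8574 = 14.3%.
- Upper bound under any dependence: 3 × 0.05 = 15%.
- Equal positive correlation r between the test statistics (simulation, 1,000,000 draws, two-sided). The article gives no correlation, so a range is shown:

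| r | 0 | 0.3 | 0.5 | 0.7 | 0.9 | 1 |
|---|---|---|---|---|---|---|
| Rate | 14.3% | 13.6% | 12.5% | 10.9% | 8.4% | 5% |

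If self-report counted as a single measure, so that there were two tests: 1 − 0.95² = 9.75% when independent.

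**3. If all three must be positive.** The false-positive rate is at most 5%. Power cannot exceed that of the weakest instrument, so it is at most the 0.8 planned for StepWatch, and it equals 0.8 only if the other two are certain to succeed whenever StepWatch does. As an illustration, three independent tests with power 0.8 each (an assumption) give 0.8³ = 0.512.

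**4. If StepWatch alone decides.** The rate is 5% and 22 per group keeps power 0.8 at the implied SD. This is the only one of the three rules under which the stated alpha and the stated power both hold.

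**5. Cost of keeping three primaries with alpha split equally.** 0.05 / 3 = 0.0167, critical value 2.394. With SD = 1,183, the standardized shift at 22 per group is (1000 / 1183) × √(22/2) = 2.804. Power = Φ(2.804 − 2.394) = 65.9% (64.6% by the t-test version). At 25 per group the shift is 2.989 and power is 72.4%. Restoring 0.8 needs 2 × (2.394 + 0.842)² × 1.3995 = 29.3, so 30 per group before drop-outs.

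**The case against.** The strongest reply is that the article already points to a lead measure. It sizes the trial for steps per day and calls that the primary outcome in the singular. It is also a condensed account: testing order, alpha allocation and the choice of questionnaire subscore are commonly left to an analysis plan, which is not shown. This stands in part. The absence of a multiplicity method is not held against the article. What remains is what it does state: a primary set of three instruments that does not match the single-variable power statement. The singular wording hints at an order but does not set one, and two other places give self-report equal rank.

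A reader might also infer that the trial's false-positive rate is in fact far above 5%. The documents do not support that, because inflation arises only if any one positive instrument counts as success, and the article states no such rule.

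A reader might go further and count more tests. Three instruments at two time points would give 1 − 0.95⁶ = 26.5% if independent (20.7% at correlation 0.5). StepWatch, AQuAA and eight CAPE scores (one overall, two domain, five type) would give 1 − 0.95¹⁰ = 40.1% (28.7% at 0.5). Neither count is in the article. It evaluates a group-by-time interaction without naming separate primary tests by time point. It describes which scores the CAPE yields, not which will be tested as primary. Social or self-improvement scores would also sit badly under a construct defined as physical activity. The article does not exclude such tests, but these figures are hypothetical and do not size this point.

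**Conclusion.** The point holds in a limited form. Primary status is shared by three instruments without an order or success rule, while the power statement covers one of them and a single unadjusted alpha applies to all.

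The consequence is conditional. Under an any-one-counts rule with one test per instrument, the rate is about 8% to 14% for correlations from 0.9 down to 0, with a ceiling of 15%. Under an all-three rule, the error rate is controlled but the stated power does not apply. The correlation, the two-sided test and the implied SD are assumptions; the mismatch between the sections is not.

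This should be fixed, but it does not undermine the design: the 22-per-group calculation survives once the outcome it was made for is named. The reliance of the other two instruments on parents who know the allocation is a further reason to settle the order before any unblinded data are seen.

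**What to change.** Name one primary outcome: mean StepWatch steps per day, analysed as the group difference in change from T0 at one prespecified time point (for example T6, the end of the intervention), tested at two-sided 0.05. The time point is needed because the sample-size statement speaks of improvement without saying when, so naming the variable alone would leave the primary test undefined.

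Make the AQuAA and the CAPE active-physical score secondary. A fixed testing order after StepWatch is optional. Treat the remaining CAPE scores as secondary or descriptive. Use the same wording in the Abstract, Procedure, Outcome measures and Statistical analysis sections.

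The change needs no extra children or measurements, and it avoids the loss of power from splitting alpha. Its cost is that a positive AQuAA or CAPE result alone can no longer make the trial positive.
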